### Inclusion criteria

1.Age range: Participants must be between 8 and 18 years old at the start of the study.2.Residency: Patients residing within the city limits of Quito, Ecuador.3.Treatment status:
•Patients are being evaluated or treated at Hospitals SOLCA and Baca Ortiz.•Patients are either currently undergoing active treatment for pediatric malignancies, or•Patients are in the post-treatment phase after a pediatric cancer diagnosis.•The volunteer or a family member that lives with the possible participant has a cellphone so the survey can be administered and answered.

### Exclusion criteria

1.The presence of a malignant solid tumor which has not yet been surgically addressed.2.A psychiatric diagnosis of cognitive impairment.3.A diagnosis of osteosarcoma.4.A history of cardiac pathology.5.The patient is in the pediatric inpatient ward or was one month prior to the enrollment phase.6.The patient is stationed at the pediatric intensive care unit.7.The patient received high-dose chemotherapy with methotrexate greater than 1,000 mg/m^2^/dose or cytarabine greater than 1 g/m^2^/dose in the last month.

### Study duration

The study is expected to last approximately 18–22 weeks in total. Recruitment of participants will be conducted over an estimated 8–12 weeks. Following the identification of both the intervention and control groups, the 10-week structured physical activity program will begin for the intervention group, while the control group will proceed without any organized physical activity intervention (Supplementary Table S2).

## Discussion

Although the study sample size is constrained by budgetary limitations and is smaller than initially calculated, this research represents a valuable first step toward evidence generation in a neglected population and geographic context. The findings will contribute preliminary insights on the feasibility, safety, and potential effectiveness of a structured physical activity program in pediatric cancer care in Ecuador. These results may serve as a foundation for designing larger multicenter trials and for informing public health policy in similar low-resource environments. A key strength of this study is its use of repeated measures, which allows for the tracking of HRQoL changes over time at multiple points (week 0, week 11, and week 24). This approach provides a robust understanding of the temporal impact of the intervention, capturing both short- and long-term benefits. Additionally, this study is the first of its kind in Ecuador, addressing a critical gap in the literature on pediatric cancer care within the region. By focusing on a structured and accessible program, this study seeks to establish a scalable model that can be adapted to meet the needs of a broader pediatric population. The ultimate goal is to inform and enhance the design of care programs that are inclusive, sustainable, and capable of significantly improving the reach and quality of care for pediatric patients, particularly in resource-constrained settings.

This research serves as a foundational step for future studies and public health initiatives, encouraging further exploration of pediatric HRQoL not only in Quito but across Ecuador. By providing evidence-based insights into the effectiveness of physical activity programs, this study offers a critical framework for developing hospital-based interventions tailored to the unique needs of pediatric cancer patients. These findings have the potential to guide the expansion of such programs at a national level, addressing the disparities in pediatric cancer care in Ecuador and beyond.

The study also emphasizes the importance of interdisciplinary collaboration. By integrating expertise from diverse fields—such as public health, oncology, social work, physiotherapy, and physical education, the research underscores the necessity of a holistic approach to pediatric care. This collaborative model ensures that care programs address not only the medical but also the social, emotional, and physical dimensions of well-being. Such a comprehensive approach is essential for fostering resilience and a higher HRQoL for pediatric patients and their families.

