## Material and methods

### Design

This study is designed as a randomized controlled trial to investigate the impact of a structured exercise program on the HRQoL of pediatric cancer patients. A total of 90 participants will be recruited and randomly assigned to either the intervention group or the control group.

The intervention group will participate in a 10-week structured physical activity program consisting of 120 min of supervised exercise per week, led by a team of physiotherapists and physical activity professionals from Hospital Sociedad de Lucha Contra el Cáncer del Ecuador (SOLCA) Quito. Meanwhile, the control group will not participate in any organized physical activity program but will continue with their usual activities. As part of the evaluation process, two versions of the Pediatric Quality of Life Inventory (PedsQL) survey will be administered: one tailored for children aged 8–12 and another for adolescents aged 13–18. Both groups will complete their respective surveys at three time points—baseline (week 0), post intervention (week 11), and follow-up (week 24). This approach allows for the assessment of changes in HRQoL over time and enables comparative analysis between the two age groups.

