### Main outcome

This research focuses on assessing the HRQoL of pediatric cancer patients, emphasizing the relationship between structured exercise programs and improvements in well-being. HRQoL is defined, as per Dac and Abhishek, as the overall well-being of individuals, incorporating both positive and negative aspects of their lives at a specific point in time (13). Key dimensions include physical, mental, and spiritual health; relationships; education; sense of security; and general well-being (13).

To evaluate HRQoL, the study will use the PedsQL, specifically the PedsQL 3.0 Cancer Module, a validated instrument for pediatric cancer patients aged 2 to 18 years. Two age-appropriate versions will be administered, one for children aged 8–12 and another for adolescents aged 13- 18. This module comprises 20 questions addressing physical, emotional, and social functioning, as well as cancer treatment-related symptoms. Participants will self-report their responses using a four-point Likert scale, with options ranging from “never” (0) to “almost always” (4). For example: “In the past month, how often have you felt tired?”; “In the past month, how often have you experienced pain or discomfort?”.

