### Statistical analysis

The data from the PedsQL surveys will first undergo descriptive analysis by age group surveys for children and adolescents. Numerical variables will be summarized as mean and standard deviation for variables with a normal distribution or median and interquartile range for non-normally distributed variables. Categorical variables will be summarized as absolute and relative frequencies. This descriptive approach will provide an overview of the data and support subsequent analyses (see Supplementary Table 2 for details on variables and survey items).

To evaluate the primary research question regarding the impact of the physical activity program on HRQoL, a bivariate analysis will be conducted. The analysis will compare exposure to the physical activity program (intervention vs. control group) and the PedsQL survey scores at different time points (week 0, week 11, and week 24). For numerical variables with a normal distribution, the Student's t-test for independent samples will be used. For non-normally distributed variables, the Mann–Whitney *U* test will be applied. Additionally, to evaluate within-group changes over time (e.g., baseline vs. end of study), paired tests will be conducted using either the paired Student's t-test for normally distributed variables or the Wilcoxon signed-rank test for non-normally distributed variables.

An intention-to-treat analysis will be employed to ensure the robustness of the results and account for potential non-compliance or missing data. This approach will analyze participants based on their initial group assignment (intervention or control), regardless of adherence to the program or completion of all study components (22).

Statistical significance will be set at *p*-value < 0.05. All analyses will be performed using R Studio (R Project version 4.3.2).

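### Within-arm change over time is tested for significance and change over time is credited to the intervention, but only the between-arm difference can support a claim of short- or long-term benefit

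*Protocol article*

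**What the plan says.** The Design section describes a randomised trial with a parallel control arm and PedsQL surveys at "baseline (week 0), post intervention (week 11), and follow-up (week 24"). The Statistical analysis section answers the primary question with a comparison between arms: "The analysis will compare exposure to the physical activity program (intervention vs. control group) and the PedsQL survey scores at different time points". As an addition it states that "to evaluate within-group changes over time (e.g., baseline vs. end of study), paired tests will be conducted", by paired t-test or Wilcoxon signed-rank test, with significance at p < 0.05. It states no between-arm comparison of change.

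The Discussion then says: "A key strength of this study is its use of repeated measures, which allows for the tracking of HRQoL changes over time". The next sentence draws the conclusion: "This approach provides a robust understanding of the temporal impact of the intervention, capturing both short- and long-term benefits".

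Three other sections bear on what a change from baseline means.
- The Inclusion criteria admit both children on active treatment and children in the post-treatment phase.
- The Exclusion criteria remove recent inpatients ("The patient is in the pediatric inpatient ward or was one month prior to the enrollment phase") and patients given high-dose methotrexate or cytarabine in the last month.
- The example items in Main outcome look back one month ("In the past month, how often have you felt tired").

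The Limitations section mentions neither natural course nor regression to the mean.

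**The concern.** A paired test inside one arm asks whether scores moved. It does not ask whether the programme moved them. In this cohort scores can move without any programme: a child who finishes treatment may recover, and a child in mid-treatment may worsen. Such movement is expected in both arms, and only the contrast between randomised arms removes it.

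Two separate paired tests, one per arm, invite a familiar error: one arm crosses p < 0.05, the other does not, and this is read as evidence that the arms differ. The Discussion's wording leaves room for that reading, because it moves from tracked change directly to the impact of the intervention. The situation is realistic here. With about 45 per arm, power for the between-arm difference of 4.36 is only about 44–45%, so a non-significant between-arm result beside a significant rise in the intervention arm is a plausible outcome. The Discussion also expects the findings to inform policy and wider roll-out.

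**Working it through.** **Inputs from the article (Sample size calculation).** SD 11.26; target difference 4.36; power 80%; 1:1 allocation; 20% loss; about 45 per arm. Allowing for the plan's loss rate, 45 × 0.8 = 36 per arm.

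**Assumed inputs, given nowhere in the article.** Two-sided α of 0.05; correlation r between baseline and follow-up of 0.5 to 0.7; a natural drift d of 2, 3 or 4.36 points, equal in both arms. The value 4.36 is borrowed from the target difference only as a familiar scale. It is not an estimate of drift.

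**The plan's own figure first.** n per arm = 2(1.96 + 0.84)² × 11.26² / 4.36² gives 105 with the normal approximation. The t-based solution is 105.67, rounded up to 106, as stated. Then 106 / 0.8 = 132.5, rounded up to 133, also as stated. The formula printed beside the SD, 15 × √(1 − 0.85), gives 5.81 rather than 11.26. That is a separate matter; 11.26 is used here because it reproduces the plan's 106.

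**Paired test in one arm with no programme effect.**
- SD of change = 11.26 × √(2(1 − r)): 11.26 at r = 0.5 and 8.72 at r = 0.7.
- Noncentrality = d / (SD of change / √n). Example: d = 3, r = 0.5, n = 36 gives 3 / (11.26 / 6) = 1.60.
- q = probability that the paired t-test is significant (noncentral t).
- The arms are independent and share the same drift, so P(intervention significant, control not) = q(1 − q).

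| Drift | n per arm | q at r = 0.5 | q at r = 0.7 | q(1 − q) at r = 0.5 | q(1 − q) at r = 0.7 |
|---|---|---|---|---|---|
| 2 | 36 | 0.18 | 0.27 | 0.15 | 0.20 |
| 2 | 45 | 0.21 | 0.33 | 0.17 | 0.22 |
| 3 | 36 | 0.34 | 0.52 | 0.23 | 0.25 |
| 3 | 45 | 0.42 | 0.62 | 0.24 | 0.24 |
| 4.36 | 36 | 0.62 | 0.83 | 0.24 | 0.14 |
| 4.36 | 45 | 0.72 | 0.91 | 0.20 | 0.09 |

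The one-arm-only pattern cannot exceed 0.25, reached at q = 0.5. It falls at the larger drift because both arms then tend to be significant together. The direction of the change follows the drift: an upward drift would look like benefit and a downward one like harm.

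**Between-arm test under the same conditions.** In simulation (10,000 trials per setting, r = 0.6, drift −4.36 to 4.36, 36 or 45 per arm, no programme effect), the t-test between arms at follow-up was significant in 4.8–5.3% of trials. Common drift leaves it at its nominal level.

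**The one-month exclusions on their own.** Suppose they remove 10–30% of patients, correlate 0.3–0.5 with the baseline score, and scores correlate 0.5–0.7 over time (all assumed). The expected later change is then about −0.2 to −1.4 points: small and downward.

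**The case against.** The strongest reply is that the plan already does the right thing. The primary question is answered by the randomised comparison at each visit, and the paired tests are introduced only as an addition and are not called evidence of efficacy. The Discussion sentence credits repeated measures in general; between-arm comparisons at weeks 11 and 24 are also repeated measures and could be what is meant by short- and long-term. The article also calls the trial a pilot and its findings preliminary. All of this stands, and it limits the point to a supporting analysis and its interpretation. It does not remove the point: the sentence before the claim speaks of tracking change, and the only stated tests of change are uncontrolled.

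A reader might go further and infer that the exclusions fix baseline as an unusually good month and so manufacture a false benefit. The documents do not support that. The exclusion windows are tied to enrolment, while the Study duration section gives 8–12 weeks of recruitment with the programme starting once both groups are identified. The month recalled at week 0 need not be the screened month. The chemotherapy exclusion bears on children on treatment, not on those past it. A selected good baseline would also push later scores down, against a claim of benefit.

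The drift sizes are assumptions. Neither the size nor the net direction of natural change can be learned from the article. That is itself the reason why uncontrolled change cannot be called programme impact.

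**Conclusion.** The point holds as a limit on inference. The plan tests within-arm change for significance, states no between-arm analysis of change, and describes change over time as the intervention's temporal impact. In a cohort of children on and past treatment, within-arm change cannot carry that claim.

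The size is illustrative. It rests on the plan's SD, 36–45 per arm, an assumed correlation of 0.5–0.7 and an assumed drift common to both arms. With no programme effect, one arm's paired test is significant in about 34–62% of trials at a 3-point drift and 62–91% at 4.36 points. Significance in the intervention arm but not in control occurs in about 23–25% and 9–24% respectively. A reader might infer from these figures that the trial's primary result is biased. It is not: common drift cancels in the randomised comparison, which keeps its 5% error rate. The risk lies in how the additional tests are read and reported.

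**What to change.** In the Statistical analysis section, make the within-arm analysis descriptive: mean change with a confidence interval in each arm, no p-value and no efficacy claim. Say that this change reflects natural course, and possibly the entry exclusions, as well as any programme effect.

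Base any statement of short-term benefit on the between-arm difference at week 11, and any statement of longer-term benefit on the between-arm difference at week 24. Describe persistence or fading by the change in that difference between the two visits, with its confidence interval. A group-by-time model would give all three, and the first two are close to what the primary analysis already does. Reword the Discussion so that temporal impact refers to these contrasts.

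The cost is wording in two sections and a little analysis on the same data. The within-arm p-values are lost; no valid claim about the programme depends on them.

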## Limitations

This study acknowledges several limitations. First, budgetary constraints prevented the recruitment of the originally calculated sample size, potentially reducing the statistical power to detect small effect sizes. Second, the study was limited to participants residing in Quito, which excluded a substantial number of eligible patients from other provinces. Third, requiring participants or their families to have access to a cell phone may introduce selection bias and limit the generalizability of findings to lower socioeconomic groups. Fourth, given the nature of the intervention and the primary outcome measure (self-reported HRQoL), blinding of participants and outcome assessors was not feasible, which may increase the risk of response and measurement bias. However, data analysis will be conducted by a researcher not involved in intervention delivery to minimize this risk. Fifth, although intervention adherence will be monitored through attendance logs and fidelity ensured through a structured protocol, individual differences in participation may still influence results. Lastly, since the study was conducted in only two hospitals in Quito, the external validity of the findings may be restricted. Future studies should consider multi-site designs and additional monitoring strategies to improve generalizability and internal validity.

## Conclusion

This study represents a significant step in addressing the HRQoL challenges faced by pediatric cancer patients. By evaluating a structured physical activity program, it provides valuable evidence to support the integration of such interventions into routine pediatric oncology care. The findings will contribute to the growing literature on pediatric HRQoL, offering practical recommendations for enhancing care programs. Ultimately, this research aims to inspire future studies and collaborations that prioritize the well-being of children with cancer, fostering better outcomes and a brighter future for this vulnerable population.
